#### Outcome measures

The primary outcome measure is the proportion of participants falling in the high risk of CVD category

The secondary outcome measures are:

i) Self-reported lifestyle changes; including changes in smoking habits, levels of exercise and fat intake[29,30]

ii): Anxiety, using the 6 item Spielberger State-Trait Anxiety Inventory (STAI)[31] and fatalism and causal attributions of heart disease using the Illness Perception Questionnaire[32,33]

iii): Perception of health-related quality of life (SF-6D, derived from SF-36, and global question 2)[34,35].

The first two groups of these measures have been used in the assessment of CHD prevention in UK primary care. Perception of health and 6 item STAI measures have been used in other studies on family history and genetic screening in primary care[21,36,37].

Qualitative interviews will be used to analyse the contextual processes that mediate lifestyle change and risk perceptions of participants identified as at high risk in both the control and the FHQ group of the study. Participants' changes in views and their perceptions of heart disease, family history, their personal risk, lifestyle, medications, ethical concerns and their social, cultural and familial context will be collected.

#### Data management

The FHQs and outcome questionnaires will be anonymised, given a unique identifier and then entered onto a database. An Access database will be specifically designed to monitor returns from each participating practice using consecutive numbering. The identifiable data will be stored securely at one site and this information will not be linked to actual socio-economic data, CVD risk assessment variables, family history and outcome measures; the unique identifier will be used for this purpose.

The Access administration database will include fields for age, gender, consent to participate, post code and sub-sample agreeing to be interviewed. Each week a printout will be generated providing details of participants who need to be contacted and sent the postal survey. The returning data will then be entered onto the main database using the participant's unique identification number.

Quality control in data entry: a 1 in 2 sample of the first 200 lifestyle outcome questionnaires at baseline and 2 weeks will be rechecked to identify errors in entry. Error rates greater than 0.5% will lead to double checking of all data entry. All CVD risk assessment scores will be checked by a second member of the team.

Interview and focus group audiotapes will be transcribed verbatim (no names or other identifying details will be included), and stored separately and securely away from transcripts.

The data will be stored for ten years on completion, in a locked filing cabinet within the researcher's employing organisational premises, in accordance with the Sponsor's requirements. Electronic data will be stored in an anonymised format and will also be encrypted.

All members of the research team will work within the principles of the Data Protection Act (1998) and Caldicott and Research Governance.

#### Sample size

The sample size for the primary outcome measure is based on the comparison of the change in the percentage of participants classified as being at high CVD risk between treatment groups. The calculation assumes that the proportion of participants at high risk will increase by 3% in the FHQ group and that there will be no increase in the standard risk assessment (control) group. Assuming a power of 80% and a two-tailed alpha of 0.05, 265 participants per group are required to detect a difference of 3%. To allow for the cluster design, an ICC of 0.01 and a cluster size of 40 are assumed. This gives a sample size of 369 participants per group completing CVD risk assessment (i.e. 10 practices per group). This is a conservative estimate since the increase in precision due to the matching of practices is not allowed for as it was difficult to find an estimate of the ICC from matched-pair data.

Further, up to 40 individuals fulfilling the "high risk" criteria, either incorporating or not incorporating family history, will be invited for qualitative interviews (this will be sufficient to reach thematic saturation in major subgroups). Focus groups will be conducted with clinicians at six practices in the FHx arm (approximately 35 individuals in total), which is also estimated to be sufficient for thematic saturation.

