#### Sample Size

The proportion of the population at high CVD risk (20% and greater CVD risk over the next 10 years) has been estimated to be at least 5%[24]. From our previous studies in which GP records were reviewed, between 3% and 13% fulfil Joint Society family history guidelines[1]. Based on this data it is estimated that the proportion of population at high CVD risk, after the inclusion of previously collected family history in the calculation, will increase by 1% to 6% (in the age group 30 to 65). To estimate an expected percentage of 6% with a two-sided 95% confidence interval extending from 3.5 to 8.5% a total of 347 participant GP manual records need to be reviewed. The small anticipated increase acknowledges the poor recording of this information, and the assumption that not all participants who are actually at higher familial risk will shift into the high CVD risk category.

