#### Data analysis

Quantitative data: Analysis will be undertaken on an intention to treat basis in that participants will be analysed in the groups to which they were allocated. The primary time point of interest is 6 months. Practices will be included in the analysis provided complete data (the outcome of interest at baseline and at 6 months follow up, and participant/practice level data that will be adjusted for in the analysis) are available for at least one of the participants recruited to the practice. Participants within the practice with incomplete data will be excluded from the analysis. If data for the secondary outcomes are missing for the 6 month assessment, a sensitivity analysis will be performed in which data from the two week assessment will be carried forward. An analysis assuming the worst case scenario of the 6 month assessment value being the same as the baseline value will also be performed.

The distribution of participants in average, moderate and high risk categories will be described by treatment group. The increase in the proportion of participants at high risk of CVD in the next 10 years as a result of incorporating systematically collected family history into CVD risk assessment score will be presented. For the primary outcome measure and the secondary outcome measures that are binary variables, the statistical significance of the difference in the event rates (e.g. the mean proportion of participants at high risk) between the FHQ and control groups will be calculated using a weighted paired t-test after the adjustment for the pairing of practices, participant and practice level variables that are associated with the outcome of interest. A weighted paired t-test will be used because it is anticipated that there will be wide variation in the number of participants recruited per practice. The robustness of the t-test will be assessed using a permutation test. Continuous outcome variables will be analysed using a similar method with differences in the mean response between the FHQ and control groups being compared using a weighted paired t-test. 95% confidence intervals will be presented for the intervention effect for all outcome measures.

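### The 80% power is calculated for a change of 0% versus 3%, but the stated primary outcome and test compare the proportion at high risk, about 5% versus 8%, where unadjusted power is about 25–32%

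*Protocol article*

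**What the plan says.** All places are in the Protocol article.

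- **Phase 2, Sample size.** The calculation is "based on the comparison of the change in the percentage of participants classified as being at high CVD risk between treatment groups". It supposes that "the proportion of participants at high risk will increase by 3% in the FHQ group and that there will be no increase" in the control group. "Assuming a power of 80% and a two-tailed alpha of 0.05", it finds that "265 participants per group are required to detect a difference of 3" per cent. For clustering, "an ICC of 0.01 and a cluster size of 40 are assumed", which gives 369 per group in 10 practices. The gain from matching is not counted, and the figure is called conservative for that reason.
- **Phase 2, Outcome measures.** "The primary outcome measure is the proportion of participants falling in the high risk of CVD category".
- **Phase 2, Data analysis.** A weighted paired t-test is applied to "the difference in the event rates (e.g. the mean proportion of participants at high risk) between the FHQ and control groups", after adjustment for the pairing and for participant and practice variables related to the outcome. None of these variables is named. The increase due to family history is to be presented, with no test attached to it.
- **Phase 1, Sample Size.** The population proportion at high CVD risk "has been estimated to be at least 5" per cent.
- **Phase 2, Study Design and Attrition rate.** Twelve pairs of practices are to be recruited, with 400 participants per arm expected to complete the risk assessment.

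**The concern.** The quantity that is powered is not the quantity that is defined as primary and tested. A change of 0% in control has no sampling variance in that arm. A proportion at high risk does, because some control participants are at high risk on the standard score alone. The same 3-point shift is therefore much harder to detect as a difference between two non-zero proportions than as 0% versus 3%.

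The stated 80% power does not carry over to the stated primary test. If the FHQ really moved 3% of people into the high-risk category, a between-arm comparison without strong covariate adjustment would more often than not be non-significant. That result could be taken as evidence that systematic family history adds little. The cost per additional high-risk individual in Phase 3 depends on the same difference.

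**Working it through.** **Inputs.** Two-sided alpha 0.05, power 80%, difference d = 0.03, ICC 0.01, cluster size 40, 369 per group (Phase 2, Sample size); 400 per arm (Attrition rate); 12 pairs (Study Design). The control rate of 5% is an assumption: it is the Phase 1 population figure, stated there as a minimum.

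**1. Reproducing the plan's figure (0% v 3%).**
- Normal approximation: n = [1.96√(2p̄(1−p̄)) + 0.842√(p₁(1−p₁)+p₂(1−p₂))]² / d². With p̄ = 0.015 this is (0.3369 + 0.1436)² / 0.0009 ≈ 257.
- At n = 265 the same approximation gives 81.3% power, and a two-sided Fisher exact test gives 80.8% (it first passes 80% at 263). So 265 is reproduced for 0% v 3%.
- A one-sided calculation with continuity correction also gives 265, again for 0% v 3%, but the text says two-tailed.
- Design effect 1 + 39 × 0.01 = 1.39, and 265 × 1.39 = 368.4, rounded up to 369. Reproduced.

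**2. The contrast that is tested (5% v 8%).**
- Variance term: 0.05 × 0.95 + 0.08 × 0.92 = 0.1211, against 0.03 × 0.97 = 0.0291 for 0% v 3%, a ratio of 4.2.
- Required n: p̄ = 0.065, so (0.6833 + 0.2929)² / 0.0009 ≈ 1,059 per arm before clustering, and 1,059 × 1.39 ≈ 1,472 after.

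**3. Power at the planned size, before covariate adjustment.** Power = Φ{[d√n − 1.96√(2p̄(1−p̄))] / √0.1211}, with n the effective size. For the paired t-test, the noncentrality is d/SE with SE² = 0.1211 × design effect / n per arm.

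| Setting | Effective n per arm | Power, 5% v 8% |
|---|---|---|
| 369 per arm, design effect 1.39, normal | 265 | 29% |
| 400 per arm, design effect 1.39, normal | 288 | 31% |
| 400 per arm in 12 practices of 33.3, design effect 1.323, normal | 302 | 32% |
| Paired t, 10 pairs of 36.9 | – | 25% |
| Paired t, 10 pairs of 40 | – | 26% |
| Paired t, 12 pairs of 33.3 (11 df) | – | 28% |

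In the last row SE = √(0.1211 × 1.323 / 400) = 0.0200, so the 95% interval is about ±2.201 × 2.00 = ±4.4 points.

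**4. Sensitivity.**
- Control rate (effective n 265, still +3 points): 38% power at 3% v 6%; 29% at 5% v 8%; 19% at 10% v 13%.
- Matching: if it removed all between-practice variance, the 12-pair t-test would have SE = √(0.1211/400) = 0.0174 and power of about 35%.

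**5. Precision of the within-person increase in the FHQ arm.** SE = √(0.03 × 0.97 × 1.323 / 400) = 0.0098. With t on 11 df, this gives 3% ± 2.2 points.

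**The case against.** **The planned test is adjusted, and the figures above are not.** This is the strongest objection and it stands in part. Data analysis adjusts for participant variables related to the outcome and requires the outcome of interest at baseline to be available. The outcome is built from the standard risk score, so a covariate close to that score would be strongly prognostic. A rough simulation with 12 pairs of 33, 5% v 8% and a latent-scale ICC of 0.01 gives about 30% power unadjusted. Power is about 38% or 49% if covariates explain 50% or 80% of the latent standard score, about 73% if they explain nearly all of it, and about 96% after adjusting for standard-score high-risk status. The covariate strengths are assumptions. A reader might infer that the trial simply has 25–30% power, or that its primary test will probably fail. The article does not support that for an adjusted test. It does not rescue the 80% either: no such covariate is named, the sample size does not rely on one, and the baseline clause is a completeness condition that does not redefine the primary outcome as change.

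**Control change may not be zero by construction.** A reader might infer that controls have only one score, so that a single reclassified FHQ participant refutes the null. The Phase 1 sections on outcome data collection and interpretation do not support that. They recalculate risk with family history already in GP records for Phase 2 participants, without limiting this to one arm, and Phase 1 expects a rise of about 1 point (5% to 6%). Zero is an assumption of the Phase 2 sample size.

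**The study is exploratory, and the increase will be presented anyway.** True, and this softens the risk of misreading. But the article still claims 80% power and names a significance test for its primary outcome.

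**Some of this belongs in a SAP.** The covariate list may. The outcome, the powered quantity and the test are all stated here, and they disagree.

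**Conclusion.** The point holds as a mismatch between three sections of the same document. The arithmetic of 265 and 369 is sound for a change of 0% v 3%, but that is neither the primary outcome as defined nor the contrast as tested. With 5% as an assumed control rate, an ICC of 0.01 and 369–400 per arm, power for the between-arm proportion before covariate adjustment is about 25–32%, against a stated 80%. Neither a control rate between 3% and 10% nor perfect matching closes the gap. The power of the adjusted test cannot be determined from the article, because it depends on covariates that are not named.

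A reader might also conclude that within-person reclassification must become primary. That goes too far: Outcome (2) compares current practice with systematic collection, so keeping the randomised comparison is equally open.

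**What to change.** Make Outcome measures, Sample size and Data analysis in Phase 2 describe the same quantity, in one of two ways.

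(a) **Change as primary.** Define the outcome as the change in high-risk status from the standard score, computed for the same person. State how the control-arm change is obtained, for example with GP-recorded family history as in Phase 1. It then need not be zero, and the 0% assumption has to be revisited. Report the FHQ increase with a practice-clustered 95% confidence interval (about 3% ± 2.2 points).

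(b) **Between-arm proportion as primary.** Name the standard risk score, or standard-score high-risk status, as an adjustment covariate. Replace the 80% claim with the power for about 5% v 8%: about 25–32% unadjusted, with the adjusted figure given under stated assumptions.

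The cost is wording only, and no new data are needed. The stated power for the raw comparison becomes much less favourable.

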#### Attrition rate

One thousand four hundred patients will be invited to participate. It is estimated that one thousand participants will complete consent and baseline questionnaire, with eight hundred completing the CVD risk assessment by having the serum cholesterol test, resulting in 400 participants recruited in each arm of the study.

Further, related to secondary outcome measures, it is estimated that 60% of recruited participants will complete the 6 month questionnaire. Hence 300 participants in each arm are expected to complete the study.

#### Data analysis

Quantitative data: Analysis will be undertaken on an intention to treat basis in that participants will be analysed in the groups to which they were allocated. The primary time point of interest is 6 months. Practices will be included in the analysis provided complete data (the outcome of interest at baseline and at 6 months follow up, and participant/practice level data that will be adjusted for in the analysis) are available for at least one of the participants recruited to the practice. Participants within the practice with incomplete data will be excluded from the analysis. If data for the secondary outcomes are missing for the 6 month assessment, a sensitivity analysis will be performed in which data from the two week assessment will be carried forward. An analysis assuming the worst case scenario of the 6 month assessment value being the same as the baseline value will also be performed.

The distribution of participants in average, moderate and high risk categories will be described by treatment group. The increase in the proportion of participants at high risk of CVD in the next 10 years as a result of incorporating systematically collected family history into CVD risk assessment score will be presented. For the primary outcome measure and the secondary outcome measures that are binary variables, the statistical significance of the difference in the event rates (e.g. the mean proportion of participants at high risk) between the FHQ and control groups will be calculated using a weighted paired t-test after the adjustment for the pairing of practices, participant and practice level variables that are associated with the outcome of interest. A weighted paired t-test will be used because it is anticipated that there will be wide variation in the number of participants recruited per practice. The robustness of the t-test will be assessed using a permutation test. Continuous outcome variables will be analysed using a similar method with differences in the mean response between the FHQ and control groups being compared using a weighted paired t-test. 95% confidence intervals will be presented for the intervention effect for all outcome measures.

Qualitative data: Interviews will be analysed using the constant comparative method[38]. Identifying emergent themes and developing the interview schedule and theory throughout the research process. It is foreseen that the qualitative project will identify psychosocial process as well as aspects of the intervention that mediate the salience of the lifestyle messages, but the open-ended nature of the interview process is designed to capture other relevant themes that emerge. The coding of the themes will be facilitated by the use of NVivo qualitative software, the thematic analysis during the research process and in the formal coding phase will be inter-rater validated between experienced qualitative researchers, supplemented by input from primary care practitioners. The analysis will also explore differences between participants from the two arms of the study, and with different socioeconomic and ethnic background. In the final stage, the qualitative findings will be triangulated with the quantitative data (including patient records) to facilitate a deeper interpretation of both data sets. Focus groups will also be analysed using the constant comparative method as described above but taking into account the conversational patterns occurring in the focus groups[28]. The topic guide of the discussion groups will focus on the feasibility and acceptability of the intervention for professionals but is open for other themes that may emerge.

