Primary prevention of CHD through lifestyle advice has sometimes yielded modest results[11] although, for example, behavioural interventions targeted at "at risk" patients have produced encouraging findings[12]. There is evidence that interventions that have targeted the family as a whole, rather than individuals, are more effective[13], and it has been reported that young individuals who were aware of their family history of CHD were less likely to smoke[14]. This evidence suggests that a family history approach, targeted at "at risk" individuals and those requesting CHD assessment, could motivate lifestyle change. However, it has been suggested that assessment of inherited risk may produce fatalism or anxiety[15], although these findings have not been corroborated in other studies[16]. Furthermore, people from different backgrounds have different understanding of the causes of heart disease; research has also discovered varied "lay models" of the risk associated with a family history of heart disease [17-19]. In light of these findings, it has been emphasized that to be effective, CHD prevention needs in-depth sensitivity to the ethnically and socioeconomically diverse patients' personal and cultural models of disease and family history [17,20]. Still, patients' interpretations of, and reactions to, incorporating family history into CHD risk assessment have not been studied. We have previously explored the psychological impact of a general family history questionnaire (FHQ)[21] and the validation of this instrument [22]. We have completed a qualitative pilot study on the feasibility of incorporating family history into CHD assessment from a risk communication point of view [23]. However, in order to inform policy the assessment of the clinical utility of using family history is now needed as a priority, alongside work such as that by the CDC Family HealthWare project, and prior to the development *de novo *of further tools[6]. This should include examination of the behavioural and psychological effects of CHD interventions using family history assessment. Moreover a better understanding of the implications of being identified as at higher risk of heart disease (due to a family history of premature CHD), for individuals from different social and ethnic backgrounds is also needed.

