### Outcome (3)

A comparison of self-reported behaviour (smoking, exercise, diet), psychological impact (anxiety, fatalism), perception of health, psychological and social experience between participants who have undergone CVD risk assessment using (i) standard risk assessment alone or (ii) standard risk assessment complemented with systematic collection of family history. [Phase 2]

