#### Data collection procedures

After initial recruitment, all participants will have their medical records reviewed to reconfirm their eligibility. On arrival of the cholesterol blood results, CVD risk scores will be calculated by the research team, as per JBS2 guidelines[1]. In the FHQ group, familial CHD risk will also be calculated and incorporated into the overall score. Two weeks after the original consultation both clinicians and participants will be sent a letter informing them about the participant's risk status. Participants identified at average or moderate CVD risk in both groups will be sent a letter confirming status together with a leaflet on lifestyle advice. In addition to a leaflet, those at higher risk in both groups will be informed that they are at higher than average CVD risk and invited for a consultation in the practice within the next 2 weeks.

In the consultation with doctor or nurse, participants will have their CVD risk explained and given lifestyle advice and, when clinically indicated, statins will be offered, as per usual practice. Participants in the FHQ group will also have the impact of premature CHD family history on the CVD risk score explained.

At two weeks and six months after the second consultation (for high risk participants) or letter being sent (for average or moderate risk participants) all participants will be posted a set of questionnaires. Participants, who have been identified at high risk, will be invited for a qualitative interview by phone, following a purposeful, maximum variation sampling strategy in terms of being in intervention or control arm, gender, age, occupational class, ethnicity, region and having or not having a family history of premature CHD. Recruitment will continue until thematic saturation is reached. Participants in the qualitative study will be interviewed by an experienced researcher in their homes (or if the participants so desire by phone) at 2 weeks and 6 months after the consultation in the practice.

Six practices in the intervention arm will be invited to participate in a focus group to capture the practitioners' views on using family history assessment and incorporate this into their clinical decision making.

After nine months the recruited participants' computer GP records will be reviewed for prescribing of: lipid lowering, anti-obesity, and anti-thrombolytic drugs, as well as nicotine replacement therapy.

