#### Ethical considerations

We do not foresee major ethical issues arising from our study. Filling the FHQ may transiently raise patients' anxiety[21], but we are recruiting patients who have either requested CVD risk assessment themselves or been offered it by their doctor, so we are not increasing anxiety in a previously unaware population. We will follow normal ethical procedures to ensure informed consent, confidentiality and data protection.

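### The anxiety comparison is fixed at 6 months, which tests persistence and could miss the short-lived rise that the protocol says is possible; a 2-week comparison should be prespecified beside it.

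*Protocol article*

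**What the plan says.** All references are to the protocol article; no SAP is at hand.

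- **Time point.** Data analysis (Phase 2): "The primary time point of interest is 6 months". No outcome is treated differently.
- **Who is analysed.** The same section requires the outcome at baseline and at 6 months and leaves out participants with incomplete data.
- **Use of the 2-week data.** For secondary outcomes with a missing 6-month value, a sensitivity analysis carries the 2-week value forward. A further analysis, labelled worst-case, sets the 6-month value equal to baseline.
- **Anxiety as an outcome.** It is part of the between-arm comparison in Outcome (3). Outcome measures lists it as a secondary outcome, measured with the six-item STAI.
- **What is expected of it.** Background notes that "it has been suggested that assessment of inherited risk may produce fatalism or anxiety" and adds that other studies did not confirm this. Ethical considerations says: "Filling the FHQ may transiently raise patients' anxiety".
- **Schedule.** Under Recruitment, the FHQ is handed out with the baseline measures. Under Data collection procedures, questionnaires go to all participants at 2 weeks and 6 months, counted from the second consultation (high risk) or from the risk letter (average or moderate risk).

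**The concern.** Six months suits smoking, exercise and diet. The Phase 3 Methods section itself says that behaviour change takes time. The same argument does not carry over to anxiety, where the article's own remark is that a rise may be brief. If the only stated between-arm comparison is late, the trial can say whether anxiety lasts but says little about whether it occurs. A null 6-month result could then be reported as reassurance about the psychological impact of family history assessment, which is a broader claim than the analysis supports.

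The missing-data rules do not close this gap. Setting a missing 6-month value to baseline is a pessimistic assumption for a lifestyle improvement. For a possible harm it assumes that nothing happened, so it pulls the comparison towards no effect.

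**Working it through.** The point is about timing, and the article gives no power figure for anxiety. The first step is to add up the schedule; the rest is an illustration of size.

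**1. Schedule, counted from the original consultation, when the FHQ is given out**

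- Risk letter: 2 weeks. High-risk consultation: within a further 2 weeks, so up to 4 weeks.
- 2-week form: 2 + 2 = 4 weeks (average or moderate risk), and up to 4 + 2 = 6 weeks (high risk).
- 6-month form: 6 months + 2 weeks, about 6.5 months; and up to 6 months + 4 weeks, about 7 months.

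The 2-week form is the earliest measurement after risk feedback and is much closer to the FHQ than the 6-month form. It is still 4 to 6 weeks away from it.

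**2. Numbers at 6 months**

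The Attrition rate section gives 400 per arm completing risk assessment, 60% of recruited participants returning the 6-month form, and 300 per arm completing. These do not all share one base: 0.60 × 400 = 240, while 300 is 0.60 × 500 (half of the 1,000 who consent). Both are used below, spread over 12 practices per arm.

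**3. Design effect**

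The formula is 1 + (m − 1) × ICC. It reproduces the plan's own primary-outcome step: 1 + 39 × 0.01 = 1.39, and 265 × 1.39 = 368.35, rounded up to 369. Applied to anxiety with the same ICC of 0.01 (an assumption):

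- 240 per arm: m = 20, design effect 1 + 19 × 0.01 = 1.19
- 300 per arm: m = 25, design effect 1 + 24 × 0.01 = 1.24

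**4. Detectable difference, 80% power, two-sided 5%**

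The formula is (1.96 + 0.84) × √(2 × design effect / n).

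- 240: 2.8 × √(2 × 1.19 / 240) = 0.28 SD
- 300: 2.8 × √(2 × 1.24 / 300) = 0.25 SD

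**5. Illustration of fading**

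The effect sizes here are assumed; the documents give none. Suppose an early rise of 0.3 SD fades by 50% to 90%: 0.3 × 0.5 = 0.15 SD, and 0.3 × 0.1 = 0.03 SD. Both lie below either detectable difference. With effective sizes 240 / 1.19 = 201.7 and 300 / 1.24 = 241.9, power is:

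| True difference | 240 per arm | 300 per arm |
|---|---|---|
| 0.30 SD | 85% | 91% |
| 0.10 SD | 17% | 20% |

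**6. What cannot be derived**

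The share of 2-week responders lost through the 6-month rule is unknown. The 40% (100% − 60%) is non-return at 6 months among all recruited participants. No 2-week response rate is given, and some non-returners will have no 2-week value either.

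**The case against.** The other side has several good arguments.

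- **Six months is defensible.** Whether anxiety lasts is a legitimate main question, and the team cites earlier work for a transient rise. This stands. Nothing in the documents requires 2 weeks to be ranked above 6 months.
- **Calling one time point primary implies others.** A condensed article may leave the 2-week comparison to the SAP, and confidence intervals are promised for all outcome measures. This stands in part: a 2-week comparison may be planned elsewhere. But the article does assign the 2-week data a role, and that role is substitution for missing values.
- **Early responders who drop out are not lost altogether.** This is correct. They leave the main analysis but return, with their 2-week score, in the carry-forward analysis. That analysis mixes early and late values, so it does not replace a comparison at 2 weeks.
- **The 2-week form may also be too late.** The transient rise is tied to filling in the FHQ, and the form comes 4 to 6 weeks afterwards. This stands as a limit of the remedy.
- **Early impact is also explored by interview** at 2 weeks and 6 months. This is true, but only in a purposive sample of high-risk participants, and it gives no estimate of the difference between arms.

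A reader might go further and infer that anxiety is measured only once the harm is expected to have gone. The documents do not support that. The article says a rise may occur, not that it will; it does not say that anxiety after risk feedback is transient; and it does collect anxiety at 2 weeks.

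**Conclusion.** The point holds as an inexpensive improvement in a secondary outcome of an exploratory trial. It does not touch the primary outcome or its sample size. As written, the stated anxiety comparison tests persistence at about 6.5 to 7 months, could miss a short-lived rise, and cannot by itself support a statement that family history assessment causes no early anxiety. The baseline-value analysis is not a worst case for this outcome.

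The detectable difference of 0.28 SD (240 per arm) or 0.25 SD (300 per arm) assumes an ICC of 0.01, which the protocol chose for the primary outcome, and makes no allowance for pairing or baseline adjustment. The 0.3 SD rise and its fading are illustrative only; the conclusion about timing does not depend on them. It would be tempting to add that up to 40% of 2-week responders are discarded, but the documents do not allow that figure.

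**What to change.** For the six-item STAI only:

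1. Prespecify a between-arm comparison at 2 weeks as a main anxiety analysis alongside the one at 6 months. Include all participants with baseline and 2-week values, whether or not the 6-month form comes back.
2. Label the 6-month comparison as a test of persistence.
3. Do not describe the baseline-value analysis as a worst case for anxiety.
4. State two limits: the 2-week form comes about 4 to 6 weeks after the FHQ and may miss the peak; and the baseline STAI is collected with the FHQ, so it may already be affected in that arm.

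Keep 6 months as the primary time point for lifestyle, illness perception and SF-6D. If the SAP already contains the 2-week comparison, it is enough to say so. The cost is a few sentences in the protocol or SAP, with no extra participants, visits or questionnaires.
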